### Randomisation

Prior to the start of recruitment, randomisation numbers will be generated by the principal investigator of the study and the project coordinator using Stata 13.2 to create an assignment schedule for block-randomisation to allocate eligible participants into one of the three study arms in a ratio of 2:3:3. Whether participants are current glucometer users or not (current vs. new glucometer users) will be used as the blocking factor, and the block size will not be communicated to study site in order to minimise the predictability of the random sequence. The project coordinator and the principal investigator of the study will then store the assignment schedule (including generation information) on a secure server at Duke-NUS. For allocation concealment, the project coordinator and a witness external to the study will enclose the assignments in sequentially numbered, opaque, sealed, randomisation envelopes and the project coordinator will hand these to the CRC along with other relevant study materials. Note that the behavioural nature of the intervention precludes masking the arm allocation to both the study team and participants. The allocation will be revealed to both the CRC and participant upon enrolment. However, the study arm assignment will be not be revealed to the laboratory staff assessing the primary outcome (HbA1c test).

### Participant recruitment, retention, withdrawal and discontinuation

Participants will either be referred by a physician from the Family Physician Clinic and General Clinic at Geylang Polyclinic, or recruited through posters advertising the study at the nine SingHealth Polyclinics in Singapore and through newspaper advertising. Prospective participants will call the CRC to schedule an appointment. If a patient is referred by a physician, the physician will verify that the patient fulfils the basic study eligibility criteria prior to referring the patient to the CRC. The CRC will either start screening the prospective participant immediately or schedule a research appointment within 2 weeks of the physician referral or at the patient’s next doctor appointment at the clinic (if any) depending on the patient’s availability. When the CRC administers the screener questionnaire, if a prospective participant answers ‘yes’ to any of the PARQ (Physical Activity Readiness Questionnaire) questions the patient will require approval from a physician before joining the study. If the patient is eligible the CRC will conduct the informed consent process and enrol the patient on to the study.

All participants will receive text messages encouraging them to remain in the study. These messages will be sent 7 days after the baseline visit as well as 28 and 56 days after the baseline and month-3 visits. Table 2 describes the text messaging schedule for all three study arms. Table 3 lists the corresponding text messages which will be automatically sent by the web application after the CRC has registered the participant during the baseline visit. To avoid any bias, all participants will receive the same number of text messages and the messages will be strictly identical except for the description of the financial incentive which is arm-specific. In addition, lost and broken devices will be replaced free of charge to enable continued participation in the study.

**Table 2 Tab2:** Text messaging schedule

Time point	SMS reminder ID		
	Arm 1	Arm 2	Arm 3
Week 1	1	1	1
Month 1	2–1	2–2	2–3
Month 2	3–1	3–2	3–3
Month 4	2–1	2–2	2–3
Month 5	3–1	3–2	3–3
Day 21 of each month where no step activity is recorded	4	4	4

**Table 3 Tab3:** List of text messages to be sent to the participants

ID	Text message
1	Dear participant, many thanks for taking part in the Trial to Incentivise Adherence for Diabetes (TRIAD) study. Please remember that regular physical activity, taking medication as recommended and monitoring your glucose level will help manage your diabetes. For assistance, please contact (clinical research coordinator (CRC’s) name) at (CRC’s contact)
2–1	Dear TRIAD participant, please remember that regular physical activity, taking medication as advised and glucose level monitoring will help manage your diabetes. You will receive SGD15 for attending the month-3 visit. You will also receive SGD90 at the end of the study for recording your data and attending the month-6 visit. For assistance, please contact (CRC’s name) at (CRC’s contact)
2–2	Dear TRIAD participant, please remember that regular physical activity, taking medication as advised and glucose level monitoring will help manage your diabetes. You will earn SGD14 weekly for meeting all activity, medicine-taking and glucose testing goals. For assistance, please contact (CRC’s name) at (CRC’s contact)
2–3	Dear TRIAD participant, please remember that regular physical activity, taking medication as advised and glucose level monitoring will help manage your diabetes. You will earn SGD14 weekly for meeting your glucose level goals. For assistance, please contact (CRC’s name) at (CRC’s contact)
3–1	Dear TRIAD participant, please remember that regular physical activity, taking medication as advised and glucose level monitoring will help manage your diabetes. You will receive SGD90 at the end of the study for recording your data and attending the month-6 visit. For assistance, please contact (CRC’s name) at (CRC’s contact)
3–2	Dear TRIAD participant, please remember that regular physical activity, taking medication as advised and glucose level monitoring will help manage your diabetes. You will earn SGD14 weekly for meeting all goals. For assistance, please contact (CRC’s name) at (CRC’s contact)
3–3	Dear TRIAD participant, please remember that regular physical activity, taking medication as advised and glucose level monitoring will help manage your diabetes. You will earn SGD14 weekly for meeting your goals. For assistance, please contact (CRC’s name) at (CRC’s contact)
4	Dear TRIAD participant, a gentle reminder that if you have not yet synced your Fitbit^TM^ you have 1 week left to sync. If you wish you can sync at the polyclinic, please contact (CRC’s name) at (CRC’s contact). Thank you

Participants will be free to withdraw their consent and discontinue their participation at any time. When possible, the CRC will administer a short exit questionnaire to inquire about the reasons of the withdrawal and collect the study devices from the participants. Further, participants will be discontinued from the study if the site principal investigator decides that continuing their participation could be harmful, or if the participant becomes pregnant. Additionally, if during the study, the participant’s condition is deemed unsatisfactory the physician may advise the patient to begin using insulin. In this case the patient will no longer be eligible for the study and will be discontinued. Participants who are discontinued from the study will receive SGD45 in compensation for forgoing potential payments that the patient might have received had they remained in the study.

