### Participant timeline and study arms

Participants in all three study arms will be issued with one Fitbit Zip™ and one eCAP™. A Fitbit Zip™ (Fitbit Inc., San Francisco, CA, USA) is a pedometer with wireless synchronisation to smartphones and computers. It tracks daily steps taken, calories burned and distance walked. An eCAP™ (Information Mediary Corporation, Ottawa, ON, Canada) is a medication-event monitoring system with an inbuilt electronic tag which records the time whenever it is closed. Participants will also use a glucometer for the study. A glucometer is a medical device that measures blood glucose levels. It is estimated that approximately half of the study participants will already use a glucometer before joining the study. Participants without a glucometer will be provided with a Nipro TRUEresult™ glucometer which they may keep after the study ends. The project coordinator will label the study devices with the participant’s unique ID number as allocated at randomisation. The clinical research coordinator (CRC) will demonstrate how to adequately use all study devices. Participants who have difficulties with their glucometer will be referred to a health counsellor at the polyclinic. Participants in all study arms will attend baseline, month 3 and month 6 assessments. At the baseline and month-6 assessments, the participants will fill out survey questionnaires (see the ‘Data collection’ section below) and take HbA1c blood tests. At the month-3 and month-6 assessments, the CRC will use the data from the three study devices to evaluate treatment adherence and the corresponding incentive payments in supermarket vouchers when applicable. At the month-18 assessment, a month-18 checklist based on participants’ medical records will be filled up by the CRC. Participants’ HbA1c blood test result since their month-6 assessment and any change in diabetes medication regimen (e.g. initiation of insulin) will be recorded. Figure 2 displays the timeline of the participants in the study.

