#### Explanatory outcomes

*Mean change from baseline in glycated haemoglobin HbA1c at months 12 and 18*

*Proportion of participants whose oral medication was titrated up at months 6, 12 and 18*

*Proportion of participants who switched to insulin therapy at months 6, 12 and 18*

*Mean change from baseline in EQ-5D-5L* [21] *score at month 6* as a measure of functional health status. This scale has been validated in people with type-2 diabetes [22]. In Singapore, both the English and Mandarin versions have been validated in people with cancer [23]
*Mean change from baseline in Brief Illness Perception Questionnaire* [24] *(BIPQ) score at month 6*. This scale has been validated in English for multiple health conditions including diabetes [25]. The Mandarin version has been validated in Taiwan in people with coronary heart disease [26]
*Mean change from baseline in Self-Monitoring of Blood Glucose* [27] *(SMBG) score at month 6*. This scale has been validated in English in people with type-2 diabetes but has yet to be validated in Mandarin and in Singapore
*Mean change from baseline in general and specific scores of the* Beliefs about Medication Questionnaire [28] *(BMQ) at month 6*. The English version of the scale has been validated for several chronic diseases including diabetes [29] while the Mandarin version has been validated in other settings such as after mechanical heart-valve replacement [30] and depression [31]. Validity in Singapore has not been established for this scale
*Mean change from baseline in the exercise subscale of the Diabetes Self-Care Activities* [32] *(DSCA) at month 6.* The English version of the scale has been pretested for acceptability and comprehensibility in a study involving people with type-2 diabetes [32] but has neither been pretested in Mandarin nor in Singapore

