### Data collection

To measure HbA1c levels for all participants, blood tests will be carried out by laboratory staff at the polyclinic at baseline and month 6. The procedure for blood tests will follow the usual polyclinic process. One of the physicians at the polyclinic will order the blood test and give a printed form to the patient. The patient will arrange and attend an appointment at the polyclinic laboratory. The laboratory technician will obtain a capillary specimen from the patient and will perform the HbA1c test on-site via the Siemens DCA Vantage® Analyzer using immunoassay. The costs of these tests will be covered by the study.

The data from the glucometers will be collected at months 3 and 6 during the clinic visits. As glucose testing is part of UC, all patients receive support for adequate usage of their glucometer. For most glucometers in use at the polyclinic (this includes the Accu-Chek Performa™, the Accu-Chek Active™ and the Nipro TRUEresult™) the device will be scanned using the appropriate docking station and the data will be downloaded to the relevant glucometer software. From the software, the data will be exported to an Excel file where the CRC will check the validity of the data. The Excel file will then be imported to the trial application where treatment adherence and the corresponding incentives will be calculated. For the less common glucometers, the data stored on the device will be manually entered by the CRC onto an Excel file which will then be imported into the trial application.

The data from the medication trackers will also be collected at months 3 and 6. The CRC will scan each medication tracker using the CertiScan™ desktop reader and the data will be downloaded to the Med-ic™ software. From the software the data will be exported to an excel file where the CRC will check the validity of the data. The Excel file will then be uploaded to the trial application where medication adherence and the corresponding financial incentives will be calculated.

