### Statistical methods

#### Primary analysis

Change from baseline in HbA1c levels at month-6 will be linearly regressed on (1) binary variables indicating the intervention arms with UC as a reference category, (2) baseline HbA1c levels, (3) a binary variable indicating titration change and (4) other baseline characteristics (gender, age, language spoken, education, occupation, income, EQ-5D-5L, BIPQ, SMBG, BMQ and DSCA scores, and binary variables indicating comorbidities) in order to increase statistical efficiency. The analysis will be performed according to an intention-to-treat approach. All missing data will be imputed using Markov chain Monte Carlo multiple imputation. To test the robustness of the results, we will carry forward the last measured HbA1c level (baseline or month 3) for those participants who withdraw from the study as those intervention participants who do not achieve their goals might disproportionally withdraw from the study. The last measured HbA1c level will also be carried forward for those participants who are discontinued from the study after switching from oral to insulin therapy.

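### Participants who start insulin leave the study with no stated month-6 HbA1c, and carry-forward refers to a month-3 HbA1c that the plan does not schedule

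*Protocol article*

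**What the plan says.** Four parts of the protocol article bear on this.

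- **Participant recruitment, retention, withdrawal and discontinuation.** If "the participant’s condition is deemed unsatisfactory the physician may advise the patient to begin using insulin", then: "In this case the patient will no longer be eligible for the study and will be discontinued". This ends participation in the study, not only in the incentive scheme.
- **Data collection** schedules the primary outcome: "blood tests will be carried out by laboratory staff at the polyclinic at baseline and month 6". **Participant timeline and study arms** agrees: "At the baseline and month-6 assessments, the participants will fill out survey questionnaires" and have HbA1c blood tests. That section uses the month-3 visit for device data, adherence and payments. The month-3 checklist, as described under Data collection, contains no HbA1c.
- **Statistical methods, Primary analysis** calls the analysis intention to treat and imputes all missing data by Markov chain Monte Carlo multiple imputation. It then adds: "To test the robustness of the results, we will carry forward the last measured HbA1c level (baseline or month 3"), for those who withdraw, because unsuccessful intervention participants may leave more often. The next sentence says that the last HbA1c "will also be carried forward for those participants who are discontinued from the study after switching from oral to insulin therapy".
- **Explanatory outcomes** lists: "Proportion of participants who switched to insulin therapy at months 6, 12 and 18". The month-18 checklist is completed from medical records.

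**The concern.** Advice to start insulin follows from unsatisfactory control, and control is what the primary outcome measures. The incentives are meant to change control, and participants and study team know the allocation. Equal rates of insulin start across arms therefore cannot be taken for granted. If these participants leave the study and no month-6 value is sought, the primary outcome is missing for a reason tied to the outcome itself, in an analysis labelled intention to treat.

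The substitute value has its own problem. Carry-forward names a month-3 measurement that the described schedule does not produce. If only the baseline exists, a carried value means a recorded change of exactly zero. Two analysts could also differ on whether insulin starters are carried forward in the main analysis or only in the robustness check, and so report different primary results.

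Last, the robustness check is meant to address selective withdrawal of participants who are doing badly. Assuming that leavers did not change cannot represent deterioration among them, so it is a weak test of that fear.

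**Working it through.** **1. The schedule against the carry-forward rule**

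| Source | HbA1c available before month 6 |
|---|---|
| Participant timeline and study arms | baseline |
| Data collection, blood tests | baseline |
| Data collection, month-3 checklist | none listed |
| Primary analysis, carry-forward | baseline or month 3 |

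With no study test after baseline and before month 6, the last value is the baseline, and change = baseline - baseline = 0. The exception is a routine clinic test. Arm 1: Usual care describes visits every 2 to 4 months with in-house HbA1c testing, so such a value may exist, but no form described in the text captures it near month 3.

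**2. Insulin starters scored as 0**

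The protocol has no figure of its own to reproduce here. Let q_U and q_I be the shares starting insulin in usual care and in the incentive arms, and x their true month-6 change, taken as the same in both. The contrast is incentive minus usual care, so negative favours incentives.

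Shift = (contrast with starters at 0) - (contrast with true values) = (q_U - q_I) × x

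Assumptions, none from the protocol: q_U 10-20%, q_I 5-10%, x = -1.2 points.

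- Smallest: (0.10 - 0.10) × (-1.2) = 0
- Largest: (0.20 - 0.05) × (-1.2) = -0.18

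Other assumptions change the sign:

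| q_U | q_I | x | Shift | Effect of incentives |
|---|---|---|---|---|
| 15% | 5% | -2 | -0.20 | overstated |
| 15% | 5% | +1 | +0.10 | understated |
| 5% | 10% | -2 | +0.10 | understated |
| 5% | 5% | any | 0 | unaffected |

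If the true change differs by arm, the shift is q_U × x_U - q_I × x_I, so it is sure to vanish only when both starts and true changes are equal.

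For scale, take the planned SD of 2 and the evaluable sizes of 51 and 152 (Sample size): SE = 2 × √(1/51 + 1/152) = 0.32. A shift of 0.18 is 0.18/0.32 = 0.56 of a standard error.

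**3. Withdrawals scored as 0, in the robustness check only**

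Take a true difference of 1.0 that would also hold among leavers, and the same share p of leavers in each arm. The estimated difference is (1 - p) × 1.0: 0.95, 0.90, 0.85 and 0.80 at 5%, 10%, 15% and 20%. The Sample size section plans for about 20% attrition.

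The planning model reproduces: 2 × [2 × (2.2414 + 0.8416)]² = 76.04 per intervention arm, stated as 76 (two-sided 2.5%, 80% power). Under that model with 90 per arm, the check's power for objective 2 at 20% leavers is about 0.75-0.77, for a comparator-arm change of -0.5 to 0. With every month-6 value retrieved and the difference still 1.0, it is 0.867.

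**The case against.** The strongest reply is that the main analysis is sound in outline. All missing data are multiply imputed, and carry-forward is introduced as a robustness test. A reader might infer that leavers in general are scored as no change in the trial's main result. The text does not support that: for withdrawals, the shrinkage from 1.0 to 0.8 belongs to the check alone.

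A reader might also infer that carry-forward for insulin starters contradicts the multiple imputation. The sentence directly follows the robustness sentence and can naturally be read as extending it. The role is ambiguous rather than contradictory. But on the milder reading the month-6 value of insulin starters is still missing for an outcome-related reason.

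Some further inferences also fail:

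- Discontinuation does not prevent insulin switches from being counted, since they can be read from medical records.
- Carry-forward is not the plan's only look at drop-out. Data management and monitoring promises an analysis of attrition and missing-data patterns, and an exit questionnaire asks for reasons. Neither tests how the estimate depends on leavers' unseen values.
- A month-3 value is not certain to be absent. Routine tests may exist, and the two schedule figures could not be seen.
- A month-6 value is not certain to be obtainable, in particular after consent is withdrawn. The month-18 checklist does not already supply it, because it covers results after month 6.

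Finally, carrying forward a pre-insulin value keeps the effect of insulin out of the comparison, which can be a legitimate aim. That stands as a reason for a labelled supplementary analysis. It does not justify leaving the outcome uncollected under an intention-to-treat label.

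**Conclusion.** The point holds in two parts. First, insulin starters are removed from the study for an outcome-related reason, with no stated collection of their month-6 HbA1c; this does not fit the intention-to-treat analysis. Second, carry-forward relies on a month-3 HbA1c that the described schedule and month-3 checklist do not provide, so without a retrieved clinic value it yields zero change. Whether carry-forward of insulin starters reaches the main analysis is left open.

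If it does, the shift is 0 to 0.18 points under the assumed rates and the assumed change of -1.2. That size and its direction rest wholly on assumptions, so a reader should not conclude that the plan favours incentives. This is a fault worth correcting, modest in likely size. No view is taken on when insulin should be started.

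**What to change.** - Reconcile the discontinuation rule, the timeline, Data collection and Primary analysis.
- Keep insulin starters in outcome follow-up where consent allows, whatever happens to their place in the incentive scheme. Obtain month-6 HbA1c by the planned test or from the clinic record, and use the observed value in the intention-to-treat analysis.
- Delete the reference to month 3, or record routine clinic HbA1c near month 3 on the checklist.
- State that multiple imputation is the main method for values still missing, for insulin starters as for others.
- Replace carry-forward as the robustness check with multiple imputation under a range of worse-than-expected shifts set separately by arm.

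The cost is revised protocol and consent wording and a small extension of the existing record checks to month 6 for discontinued participants; on-site testing and record access are already in place. The estimated effect will then include the effect of insulin use, so carry-forward or another pre-insulin analysis may be kept as a labelled supplementary analysis. The clinical decision on insulin is untouched.

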### Data collection

To measure HbA1c levels for all participants, blood tests will be carried out by laboratory staff at the polyclinic at baseline and month 6. The procedure for blood tests will follow the usual polyclinic process. One of the physicians at the polyclinic will order the blood test and give a printed form to the patient. The patient will arrange and attend an appointment at the polyclinic laboratory. The laboratory technician will obtain a capillary specimen from the patient and will perform the HbA1c test on-site via the Siemens DCA Vantage® Analyzer using immunoassay. The costs of these tests will be covered by the study.

The data from the glucometers will be collected at months 3 and 6 during the clinic visits. As glucose testing is part of UC, all patients receive support for adequate usage of their glucometer. For most glucometers in use at the polyclinic (this includes the Accu-Chek Performa™, the Accu-Chek Active™ and the Nipro TRUEresult™) the device will be scanned using the appropriate docking station and the data will be downloaded to the relevant glucometer software. From the software, the data will be exported to an Excel file where the CRC will check the validity of the data. The Excel file will then be imported to the trial application where treatment adherence and the corresponding incentives will be calculated. For the less common glucometers, the data stored on the device will be manually entered by the CRC onto an Excel file which will then be imported into the trial application.

The data from the medication trackers will also be collected at months 3 and 6. The CRC will scan each medication tracker using the CertiScan™ desktop reader and the data will be downloaded to the Med-ic™ software. From the software the data will be exported to an excel file where the CRC will check the validity of the data. The Excel file will then be uploaded to the trial application where medication adherence and the corresponding financial incentives will be calculated.

Each pedometer will be linked to an anonymous online Fitbit™ account that will be created for the study. The trial application will automatically synchronise with the Fitbit™ accounts and automatically update physical activity data for adherence and incentives calculations. This data will be checked regularly by the project coordinator to verify that the participants are synchronising their pedometer with their Fitbit™ account and that this data gets transmitted to the trial application. This is important because the pedometers can store up to 30 days of data. Participants who do not synchronise for 21 days will receive an automatic text message to remind them to synchronise. Participants who do not have access to a smartphone or personal computer will need to come to the polyclinic once a month where the CRC will synchronise their pedometers for them.

Paper-based survey questionnaires will be administered at baseline and month 6 by the CRC. Both questionnaires include the European Quality of Life-5 Dimensions-5 Levels,(EQ-5D-5L), BIPQ and BMQ survey instruments. The baseline survey also includes patient socioeconomic characteristics while the month-6 questionnaire contains questions on compliance with the medication tracker and medication-purchasing habits during the intervention period.

In addition, the CRC will complete participant checklists at baseline, months 3, 6 and 18. The Baseline checklist will include the participant’s current HbA1c reading and the date of the blood test. This information will be obtained from the SingHealth computerised patient database at Geylang Polyclinic. The randomisation code and study arm, the participants’ diabetes medication regimen, and whether the participants are new or current glucometer users will also be recorded on the checklist. The CRC will also confirm the participants have understood which study arm they have been randomised to, record the response on the checklist and explain again if necessary.

At months 3 and 6, the CRC will again check that the participant understands the goals and rewards of the study arm they have been randomised to, record the response on the corresponding checklist and re-explain if necessary. Details on fasting which could affect medication dosages and times; overseas trips which involve time zone changes that will possibly impact the study devices; and hospitalisations will also be recorded at months 3 and 6. Further, the participants’ adherence and payments made will be recorded along with the time spent by the CRC on adherence calculation and corresponding incentive payments. Last, the CRC will record any changes to the participants’ diabetes medication regimen based on their medical records.

At month 18, the CRC will complete a checklist solely from the patient’s medical records. This checklist will include recording HbA1c results and any changes in medication regimen since the patient completed the intervention.

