### Explanatory analyses

The same model as for the primary analysis will be conducted with changes from baseline in HbA1c levels at months 12 and 18. Logistic regressions of binary variables indicating whether the participants have had a titration change of their oral medicine, and whether they have switched to insulin therapy at months 6, 12 and 18 will be estimated. Linear regressions of the changes from baseline in EQ-5D-5L, BIPQ, SMBG, BMQ and DSCA scores at month 6 will also be estimated. For all models, the covariates will be binary variables indicating the intervention arms and the same other baseline characteristics as for the primary analysis. Next, the models used in the primary and secondary analyses will be extended by adding interaction terms between potential intervention moderators (gender, age, language spoken, education, occupation, income, EQ-5D-5L, BIPQ, SMBG, BMQ and DSCA scores, and binary variables indicating comorbidities) and the binary variables indicating study arms. In particular, this analysis will be used to determine the benefit incidence of the intervention according to socioeconomic factors.

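### The month-18 record review is worded to start at the end of the intervention, so later HbA1c and regimen records of participants who leave before month 6 are not provided for

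*Protocol article*

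**What the plan says.** All references are to the protocol article.

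**Source of the late data.** Under Data collection: "At month 18, the CRC will complete a checklist solely from the patient’s medical records". No visit or device is involved, and no other data collection after month 6 is described.

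**Window of the review.** The same section continues: "This checklist will include recording HbA1c results and any changes in medication regimen since the patient completed the intervention". The section Participant timeline and study arms gives a matching window: "Participants’ HbA1c blood test result since their month-6 assessment and any change in diabetes medication regimen (e.g. initiation of insulin) will be recorded".

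**Who leaves before that window opens.** The section on recruitment, retention, withdrawal and discontinuation deals with participants advised to start insulin during the study: "In this case the patient will no longer be eligible for the study and will be discontinued". On withdrawal it says: "Participants will be free to withdraw their consent and discontinue their participation at any time". It does not say whether records may still be consulted after either event.

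**What is to be analysed.** The Explanatory outcomes include HbA1c change at months 12 and 18, upward titration of oral medication at months 6, 12 and 18, and this: "Proportion of participants who switched to insulin therapy at months 6, 12 and 18". None is limited to completers. Under Explanatory analyses: "The same model as for the primary analysis will be conducted with changes from baseline in HbA1c levels at months 12 and 18". The primary analysis is by intention to treat with multiple imputation. It also describes carrying forward the last measured HbA1c, both for withdrawals (as a robustness check) and for participants discontinued after switching to insulin.

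**The concern.** The collection window does not match the outcomes it has to serve. The outcomes are defined for the randomised sample at months 12 and 18. The window is anchored to an event, completion or the month-6 assessment, that early leavers never reach.

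The same clinical event is also followed up differently according to its date. If insulin is started after month 6, the start and the later HbA1c fall inside the review. If it is started before month 6, the participant is discontinued and nothing in the text provides for later HbA1c or regimen records.

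The absence is unlikely to be random. Insulin is advised when a participant's condition is judged unsatisfactory. The Primary analysis section itself expects that intervention participants who miss their goals may withdraw more often. At stake is whether the long-term arm comparisons rest on observed values or on substitutes for a group selected by poor control.

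**Working it through.** **1. The passages side by side.**

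| Participant | Month-18 window as worded | Later HbA1c and regimen provided for? |
|---|---|---|
| Completes month 6, no insulin | Opens at month 6 | Yes |
| Completes month 6, then starts insulin | Opens at month 6 | Yes; insulin start is a named example |
| Starts insulin before month 6, discontinued | No starting point | No |
| Withdraws before month 6 | No starting point | No; also depends on consent to record access |

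**2. The plan's own figures, which give the planned attrition.** The Sample size section uses SD 2, a difference of 1 percentage point, two-sided alpha 0.025 and 80% power.
- Each intervention arm: 2 × [2 × (z for alpha 0.025 + z for power 0.80) / 1]² = 76.04, against the plan's 76.
- UC arm, against 152 incentive participants: K = 76.04 / 2 = 38.02, and 1 / (1/38.02 − 1/152) = 50.7, rounded up to the plan's 51.

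These reproduce. The plan then enrols 60 + 90 + 90 = 240, citing about 20% attrition. No sample-size figure is in dispute here.

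**3. How many could be affected.**
- At 20%: 0.20 × 240 = 48 (12 in UC, 18 in each incentive arm).
- At 15%: 0.15 × 240 = 36.
- At 10%: 0.10 × 240 = 24.

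This is a ceiling on what better wording could recover. The allowance does not separate withdrawals from discontinuations, and some who withdraw may refuse further use of their records. The documents give no rate of insulin start. Assuming 2% to 10% before month 6, it would be 0.02 × 240 = 4.8 to 0.10 × 240 = 24 participants.

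**4. What would stand in for the missing HbA1c.** Study HbA1c tests are scheduled at baseline and month 6 only. The Primary analysis section allows for a month-3 value, but no study test is scheduled then, although routine care could supply one. Unless a routine result is used, the last measured value for an early leaver is the baseline value. Carried to month 18, it gives a change of exactly zero, whatever the chart shows. The article does not say whether carry-forward extends to months 12 and 18; if it does not, multiple imputation fills the gap.

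**5. Whether real values are likely to exist.** The usual-care section describes follow-up every 2 to 4 months and an HbA1c laboratory in every polyclinic. Results are therefore plausible for leavers who remain patients there, but the documents do not show how many do.

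**The case against.** The strongest reply is that the text fixes a time window, not a population. The article says that the coordinator completes checklists at baseline and months 3, 6 and 18 without limiting them to completers, and the analyses carry no such limit either. Record access after leaving may be settled in the consent form or the full protocol, which are not shown. This stands in part: a reader might infer that leavers' charts are excluded, and the document does not say that. But it is not merely silent. It states the start of the window twice, and both times the start is an event that leavers do not reach.

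Three stronger readings are tempting and are not supported.

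- **That the insulin comparison is hidden.** Assume that 15% of UC and 12% of an incentive arm switch by month 18, with 6 and 3 points of this before month 6. Dropping early switchers from numerator and denominator gives 9/94 = 9.6% against 9/97 = 9.3%, a difference of 0.3 points instead of 3.0. The plan states no such exclusion. An early switch is known because it is the reason for discontinuation; counting it restores 15% against 12%. The rates are also invented for illustration.
- **That regimen changes before month 6 are never captured for leavers.** The month-3 and month-6 checklists take these changes from medical records, and the text does not make this depend on attendance.
- **That 48 participants are an avoidable loss.** That figure is a planning allowance and includes people who may withdraw consent.

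It is also fair to say that analysing HbA1c measured on insulin is a choice of estimand, and that the plan's carry-forward is not shown to be an error. That argues for collecting the values and reporting both analyses, not for replacing one with the other.

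**Conclusion.** The point holds as a gap in what is collected. As worded, the plan does not provide for HbA1c and regimen records after leaving for participants who withdraw or are discontinued before month 6, while its month-12 and month-18 outcomes cover everyone randomised. Up to 48 of 240 could be affected at the planned attrition (24 to 36 at 10% to 15%). The recoverable number is smaller and cannot be derived from the documents.

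The conclusion assumes that the two window statements are applied literally, that leavers differ in glycaemic control, and that some continue to have HbA1c measured in routine care. The direction and size of any bias in the arm comparison cannot be determined. The affected outcomes are explanatory; the month-6 primary result does not depend on this checklist. The change is still worth making, because an analysis plan cannot recover records that were never extracted.

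**What to change.** Reword both descriptions of the month-18 checklist (Participant timeline and study arms; Data collection) so that it is completed from medical records for every randomised participant. This includes those discontinued and, where consent to record access continues, those withdrawn. It should cover HbA1c results and dated regimen changes from randomisation.

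Under Explanatory outcomes, state that an insulin start before month 6 counts as a switch at months 6, 12 and 18. Collect HbA1c recorded after an insulin start, so that the month-12 and month-18 analyses can be run with it alongside the planned carry-forward. None of this alters any treatment or discontinuation rule.

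The cost is protocol wording, up to about 48 further chart reviews by the existing coordinator, and a consent-form line on record access after leaving. Participants who refuse such access stay missing. The Trial status section reports 140 of 240 enrolled and recruitment still open, and charts can be read retrospectively where consent allows, so the change remained feasible at that point.
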